### Procedures

#### Screening visit

At screening each patient will undergo a physical examination including measurements of height, weight, pulse and blood pressure. Additional investigations will include electrocardiography, urine dipstick and laboratory blood tests. Women of childbearing potential must have a negative pregnancy test at the screening visit and should use accepted highly effective contraceptive methods.

#### Allocation/randomization

After inclusion, baseline measurements will take place at the University Medical Center Groningen (UMCG). The study drugs (ambroxol and placebo) will be identical in appearance. The capsules will be supplied in brown glass bottles and will only be identifiable by the randomization number. Subjects will be randomized using block randomization and are stratified by sex and disease duration at time of inclusion (0–5 years and 5–10 years). Disease duration will be defined in years and months. ALEA Clinical software will be used for random assignment to placebo or ambroxol [63].

#### Unblinding

Breaking the blind will occur for any participant experiencing a serious adverse event (SAE) for which the clinical management of the SAE will be facilitated by the unblinding of the patient’s treatment allocation. The Principal Investigator (PI) will determine if the patient should be unblinded. All SAEs that are related to the trial medication and are suspected to be unexpected, are submitted to the regulatory agencies within pre-specified timelines. If deemed necessary by the investigator, an unscheduled visit can be performed to discuss study drug discontinuation and the importance of subsequent follow up. As participation in the trial is entirely voluntary, the patient may choose to discontinue trial treatment at any time without any consequences.

### Data collection and monitoring

Patient data are stored in an electronic Case Report Form (eCRF). Data collected during visits will also be stored as a hard copy and will be kept in a file cabinet. Other data, unfit for storage in de eCRF, will be collected in protected servers of the UMCG. All data and documents that are collected during the study will be processed in coded format, with the exception of the Informed Consent Form, on which name and date of birth of the patients are written down.

For a 6-monthly review of study processes, a Data and Safety Monitoring Board (DSMB) has been appointed.

### Statistical analyses

All statistical tests will use an alpha of 0.05, with two-way testing. Data will be analyzed according to the intention-to-treat principle, which will include all patients having completed at least 1 post-randomization follow-up visit. A summary of baseline characteristics and the outcomes at baseline at subsequent treatment-phase visits for the whole cohort will be presented as point estimates with their standard deviations, or as counts and percentages where the data are categorical. Baseline characteristics will be summarized per randomization group.

Primary outcome analyses will evaluate the impact of treatment allocation (ambroxol or placebo) on the difference between MDS UPDRS part III OFF medication scores at 60 weeks follow up. A regression analysis of covariance (ANCOVA) approach will be used to analyze the effect of ambroxol. This is done to adjust for stratification factors and baseline MDS-UPDRS part III values. Also, post-hoc analysis will determine eventual effects of changes in LED on the primary outcome.

Secondary continuous outcomes will be analyzed using regression analyses as well, also adjusting for stratification factors and baseline scores. Comparison of adverse events between treatment groups will be done with χ^2^ tests.

Post-hoc analysis will be performed to correlate GCase activity at baseline and at 60 weeks with MDS-UPDRS III scores. Additionally, the effect of ambroxol on pathological (i.e. severe and mild) GBA variants specifically will be analyzed post-hoc.

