## Methods/design

### Trial design

This study is a randomized, placebo-controlled trial with ambroxol in non-demented PD patients with a proven GBA mutation. This study is reported following the SPIRIT guidelines (see Supplementary file 1) [45].

This is a single-center trial carried out in the University Medical Center Groningen, with ambroxol versus placebo during 48 weeks, followed by an open 12-week washout period, creating an overall duration of 60 weeks. During these 48 weeks, patients will receive either ambroxol 1800 mg/day or placebo. This includes a 3 week titration period, in which the dose will be increased with 600 mg/day every week. The primary endpoint is the change in off-period scores of the Unified Parkinson’s Disease Rating Scale of the Movement Disorder Society (MDS-UPDRS) part III between baseline and 60 weeks, including a 12-week wash-out period, to exclude an unlikely therapeutic effect of ambroxol. Secondary endpoints are also compared between baseline and 60 weeks, and include safety/tolerability of ambroxol, change in GCase activity in monocytes, striatal F-DOPA uptake as measured by [18]F-DOPA PET scans of the brain, resting state fMRI, related to structural MRI and diffusion tensor imaging (DTI) tractography, quality of life (QoL), measured by the Parkinson’s Disease Questionnaire-39 (PDQ-39), the presence and severity of non-motor symptoms using the Non-Motor Symptoms Scale (NMSS), cognitive changes measured by the MOCA and finally the changes in Levodopa equivalent doses (LED). For an overview of study visits, see Fig. 1.

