### Outcomes

The primary endpoint of this study is the change in the MDS-UPDRS part III motor subscale in the practically defined OFF medication state between baseline and 60 weeks. The MDS-UPDRS part III is a motor scale using a score range from 0 to 132 points, with 0 indicating no disability and 132 indicating total disability. All 18 items are evaluated on a five-point scale from 0 to 4. All items contain clearly formulated instructions for both the patient and the investigator [46, 48]. MDS-UPDRS part III in OFF medication state will be assessed every 12 weeks. OFF medication state is defined as withdrawal from dopaminergic medication for at least 8 hours. To ensure the reliability of the UPDRS III scores, several measures were implemented. First, all examiners had to pass the formal MDS-UPDRS training. All MDS-UPDRS III assessments are video recorded and scored by or together with the main co-investigator.

The study has several secondary endpoints, which are also comparing data at 60 weeks versus baseline scores. The following secondary endpoints will be assessed during this study.

*[*
^*18*^
*F]F-DOPA PET*

The PET tracer [^18^F]F-DOPA PET binds to aromatic amino acid decarboxylase (AADC) and estimates the rate of decarboxylation of [^18^F]F-DOPA to [^18^F]fluorodopamine which corresponds to striatal dopamine production and is considered a reliable tool to assess nigrostriatal dopamine synthesis capacity in vivo [49]. The PET-scan is performed after at least 6 hours of fasting (4 hours for diabetic patients). Participants are premedicated with carbidopa, 60 minutes before receiving 200 MBq of the F-DOPA tracer. The F-DOPA PET scan is performed 90 minutes after injection of the tracer on a Siemens HR+ camera. [^18^F]F-DOPA PET will be performed at baseline and at 60 weeks, to analyze the change in striatal activity. [^18^F]FDOPA striatal-to-occipital ratios of the putamen and caudate nucleus will be calculated to quantify the striatal dopaminergic innervation.

*MRI*

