Side-effects and other AEs will be monitored closely during the trial. For the first 3 weeks, during the titration phase, participants will receive a phone call once a week to assess possible side-effects. They will be asked to report openly first and will then be read out a selection of specific known side-effects of ambroxol to assure thorough reporting. All AEs will be followed until they have abated, or until a stable situation has been reached. Depending on the event, follow up may require additional tests or medical procedures as indicated, and/or referral to the general physician or a medical specialist.

*Other study parameters*

This study will register also the following items to characterize the study population and to monitor side effects.Demographics, including age at onset of PD, sexLEDIntoxications: alcohol and drug useIntake: six-monthly food diary entailing the last weekMedical history:General medical historyNeurological comorbidityMedical family history

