## Discussion

This study aims to investigate the disease-modifying properties of high-dose ambroxol in PD patients with a GBA mutation. MDS-UPDRS part III in dopaminergic OFF-state is used as the primary outcome measure to investigate the possible disease-modifying effect of ambroxol. Although not perfect, this still is one of the best clinical tools to monitor disease progression [64, 65], in this trial accompanied by imaging markers as well.

Measuring GCase activity in vivo is also a matter of ongoing debate, including the lack of understanding on the precise role of the sphingolipid metabolism and its relationship to PD progression. Our current approach has implemented the most recent findings on sphingolipid metabolism in PD-GBA mutants, using PBMCs (monocytes) and serum sampling [33, 54]. Our sampling strategy represents the major metabolic routes of SLs.

Also, safety and tolerability monitoring are important outcome measures of this study. Side-effects are closely monitored, with extra visits during the titration phase. This allows the investigators to take action on short notice. However, based on previous research, ambroxol has not shown significant safety issues [39, 41, 42].

All PD patients that carry a GBA mutation are allowed in this study. This means that severe, mild and risk variants are included, as well as variants of unknown significance. Based on previous research, it is to be expected that the majority of subjects will be carrier of a risk variant [10]. A post-hoc analysis will be carried out to analyze the effect of ambroxol focused on pathogenic mutations specifically.

Our study uses a washout design, including a 12-week washout period, to eliminate any symptomatic effect of ambroxol.

This trial makes use of capsules, containing 600 mg of ambroxol, which will improve the tolerability and compliance of this treatment.

This is a single-center study, which will improve the homogeneity of the study population. The nation-wide screening in the Netherlands, now complemented with an additional population-wide screening, has resulted in large numbers of PD patients with a known GBA status. There will be an overrepresentation of participants from the northern part of the Netherlands, because the additional screening will take place especially in the neurology practices in the northern counties of the Netherlands.

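### The set called intention-to-treat leaves out randomised patients with no post-randomisation visit, which can bias the primary comparison and, on a plain reading, the adverse-event comparison

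*Protocol article*

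**What the plan says.** All places are in the protocol article.

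- **Analysis set (Statistical analyses):** "Data will be analyzed according to the intention-to-treat principle, which will include all patients having completed at least 1 post-randomization follow-up visit". The primary ANCOVA and the secondary regressions follow in the same section, as does the safety comparison: "Comparison of adverse events between treatment groups will be done with" chi-squared tests. No other analysis set is named.
- **Status of safety (Trial design):** "Secondary endpoints are also compared between baseline and 60 weeks, and include safety/tolerability of ambroxol".
- **Titration (Trial design):** "This includes a 3 week titration period, in which the dose will be increased with 600 mg/day every week".
- **Contact during titration (Outcomes, Safety):** "For the first 3 weeks, during the titration phase, participants will receive a phone call once a week to assess possible side-effects". The Discussion puts it differently: "Side-effects are closely monitored, with extra visits during the titration phase".
- **Primary scale (Outcomes):** "MDS-UPDRS part III in OFF medication state will be assessed every 12 weeks". In the text, the first post-baseline score therefore falls at week 12.
- **Missing data:** last observation carried forward (LOCF) for all missing values.

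**The concern.** Intention-to-treat keeps every randomised patient in the arm to which they were allocated. A requirement of one completed follow-up visit removes patients because of something that happened after allocation. If some ambroxol patients cannot tolerate the rising dose and leave the study in the first weeks, they are removed from one arm for a reason related to treatment. What remains is no longer a fully randomised comparison.

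Two results are at stake. The estimated difference in MDS-UPDRS III then describes patients who stayed long enough to be seen, not all who were randomised. The adverse-event comparison, which serves a named secondary endpoint, would lose the patients who say most about the tolerability of titration, even though their events may already have been reported by phone.

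**Working it through.** **Inputs.** From Sample size and power calculation: expected placebo change 3.91, ambroxol change 0, common SD 6.1, two-sided alpha 0.05, power at least 80%, 80 patients. From Study population: 80 patients to be included. The allocation ratio is not stated; I assume 1:1, so 40 per arm. No early drop-out rate is given, so every count of leavers below is an assumption.

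**Step 1: the plan's own figure.** n per arm = 2 × (1.960 + 0.842)² × 6.1² / 3.91² = 38.2, so 39 per arm and 78 in total. The t-test calculation gives 39.2, so 40 per arm and 80 in total. The stated 80 is reproduced, with t-test power of 80.8% at 40 per arm.

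**Step 2: effect on the estimated difference.** Let k of 40 ambroxol patients leave before any visit and then progress as placebo (change 3.91), while the other ambroxol patients have change 0. No placebo patient leaves.

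- All randomised: difference = 3.91 × (40 − k) / 40.
- Set as stated: the leavers are dropped, so the difference stays at 3.91.

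| k | All randomised | Set as stated | Hidden by exclusion |
|---|---|---|---|
| 0 | 3.91 | 3.91 | 0 |
| 2 | 3.71 | 3.91 | 0.20 |
| 4 | 3.52 | 3.91 | 0.39 |
| 6 | 3.32 | 3.91 | 0.59 |
| 8 | 3.13 | 3.91 | 0.78 |

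**Step 3: effect on adverse events.** Let the same k patients each leave because of an adverse event, with no such event in any other patient.

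| k | All treated | Uncorrected chi-squared p | Fisher p | Set as stated |
|---|---|---|---|---|
| 4 | 4/40 (10%) vs 0/40 | 0.040 | 0.116 | 0/36 vs 0/40 |
| 6 | 6/40 (15%) vs 0/40 | 0.011 | 0.026 | 0/34 vs 0/40 |

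For k = 4, the uncorrected statistic is 80 × (4 × 40 − 36 × 0)² / (40 × 40 × 4 × 76) = 4.21. The p-value depends on the test chosen. What does not depend on it is that the whole imbalance disappears from the analysed data.

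**Step 4: would LOCF repair an all-randomised set?** No. With no post-baseline score, LOCF carries baseline forward, which records a change of 0. That is the change assumed for ambroxol. For k = 4 the ambroxol mean is (36 × 0 + 4 × 0) / 40 = 0, and the difference is again 3.91, the same as after exclusion.

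**Step 5: power.** Dropping 4 ambroxol patients gives t-test power of 78.6%. Keeping them, with progression as placebo, gives 72.2%, because the difference to be detected is 3.52. The exclusion therefore costs less power than full inclusion does, and power is no argument for the change.

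**The case against.** **The group at risk may be small.** The rule turns on attending no follow-up visit, not on stopping capsules. Someone who stops in week 2 and attends any later visit stays in. The Discussion mentions extra visits during titration, and the Unblinding section allows an unscheduled visit when drug discontinuation is considered. If such visits count, some early leavers are retained. Follow-up visit is not defined in the text, and the visit figure is not shown. All of this stands: it limits the number affected, but it does not make the set intention-to-treat.

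**The safety part is partly inference.** The text does not say that early leavers' events are discarded, and a safety set may be defined in a full protocol or analysis plan not shown here. That also stands. The point is limited to the plain reading: the rule is stated for the data in general, and the adverse-event tests follow under it.

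**Stronger readings are tempting and not supported.** A reader might infer that everyone who stops during titration is lost, that harm will certainly be understated, or that the trial will lose its power. The documents give no early drop-out rate, the rule does not exclude those who only stop the drug, and step 5 shows that power points the other way. A reader might also rest the case on a p-value crossing 0.05. With 4 vs 0 events the uncorrected test gives 0.040 but Fisher's test gives 0.116, so that is too fragile.

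**Imputation adds little information.** Multiple imputation from the patient's own arm would leave the estimate close to 3.91 in the example. This is fair, and it is why the fix adds a sensitivity analysis that imputes from the placebo arm.

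**Conclusion.** The concern holds in a limited form. The label and the definition in the same sentence contradict each other: the set is a modified intention-to-treat set whose membership treatment can affect. This is a stated rule and not a detail left open.

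The harm is possible bias in the estimated difference and possible understatement of adverse events. Its size cannot be known from the article. With 2 to 8 ambroxol leavers out of 40, none on placebo, and leavers progressing as placebo, the reduced set hides 0.20 to 0.78 points of a planned 3.91. With 4 leavers, a 10% vs 0% imbalance in adverse events becomes none. If nobody leaves before a first visit, nothing changes. If leavers are few and balanced between arms, the effect is small. The adverse-event part further assumes that no separate safety set exists elsewhere.

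**What to change.** 1. **Primary efficacy set:** all randomised patients, analysed as allocated.
2. **Patients with no post-baseline score:** multiple imputation instead of LOCF, ideally with a sensitivity analysis that imputes ambroxol leavers from the placebo arm. The ANCOVA with stratification factors and baseline can stay as the analysis model.
3. **Adverse events:** compare in all patients who took at least one capsule, and include events reported in the titration phone calls. If a separate safety set already exists in another document, refer to it here.
4. **Wording:** if the present set is kept as a supportive analysis, call it modified intention-to-treat and define follow-up visit. Reconcile the phone calls in Outcomes (Safety) with the extra visits in the Discussion.

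**Cost:** no new data, since baseline scores and phone reports are already collected. Imputation needs some added specification and analysis work. The estimated effect may come out smaller, and power lower, than in the reduced set; in the example with 4 leavers who progress as placebo, 72.2% against 78.6%.

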**Discussion:**

Ambroxol up to 1200 mg/day has shown effects on human cerebrospinal fluid endpoints, which supports at least passage of the blood-brain-barrier. The dose titration in this trial up to 1800 mg/day will reveal if this dose level is safe and also effective in modifying the course of the disease.

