### Study population

In total, 80 GBA-PD patients will be included in this trial. In order to be included, subjects must have been diagnosed with PD according to Movement Disorders Society (MDS) criteria [46].

Patient’s should have a disease duration of under 10 years at inclusion, and they should be proven carriers of a GBA mutation. Subjects who are unable to undergo an MRI scan or have Deep Brain Stimulation (DBS) are excluded from this study. For a detailed overview of the in- and exclusion criteria, see Table 1.

**Table 1 Tab1:** In- and exclusion criteria

Inclusion criteria	Exclusion criteria
Diagnosis of PD	Refusal to be informed about an unforeseen clinical finding
Disease duration of < 10 years	Use of DBS
Proven carrier of GBA-mutation	Confirmed dysphagia
Able to write written informed consent	Known sensitivity to study medication
Able to understand protocol	MRI incompatible implants in body
Able to self-administer oral ambroxol	Pregnant or breastfeeding
	Clinically significant medical or surgical condition

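### The article promises to reveal whether 1800 mg/day is safe, but its only stated between-arm safety analysis is a χ² difference test that, at about 40 per arm, often misses a doubling of uncommon adverse events

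*Protocol article*

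**What the plan says.** The abstract's Discussion paragraph states: "The dose titration in this trial up to 1800 mg/day will reveal if this dose level is safe and also effective". Trial design lists safety among the secondary endpoints: "Secondary endpoints are also compared between baseline and 60 weeks, and include safety/tolerability of ambroxol". The main Discussion repeats the emphasis: "Also, safety and tolerability monitoring are important outcome measures of this study".

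The section Statistical analyses gives the method for comparing arms: "Comparison of adverse events between treatment groups will be done with χ^2^ tests". The general rule at the head of that section applies to it: "All statistical tests will use an alpha of 0.05, with two-way testing". No effect measure, interval or expected event rate accompanies the test.

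The trial size comes from Study population, "In total, 80 GBA-PD patients will be included in this trial", and was set on the MDS-UPDRS part III change alone (Sample size and power calculation).

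**The concern.** A difference test answers whether the arms differ by more than chance would explain. It does not answer whether the dose is safe. In a trial sized on a motor score, a p-value above 0.05 is the likely result for an uncommon adverse event even if ambroxol doubles its rate. A report of no significant difference, set beside the abstract's promise, could then be taken as the promised answer, although the same counts would leave a large excess open.

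This matters more because the Parkinson's disease study cited under Dose selection used 1260 mg/day, and the sample-size section describes that same reference as 17 patients treated for 186 days without a control group. Dose selection also cites higher mg/kg exposures, but these were for pneumonia, intravenous, or in children for 10 days. For 48 weeks at up to 1800 mg/day in this population, the trial's own controlled comparison is the key evidence.

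**Working it through.** **Inputs from the article.** Total 80 patients (Study population); two-sided alpha 0.05 and a χ² test (Statistical analyses); difference 3.91, SD 6.1, power at least 80% (Sample size and power calculation).

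**Assumptions.** Allocation 1:1, so 40 per arm, since the allocation section states blocks and strata but no ratio. Full follow-up. The outcome is patients with at least one event. Pearson χ² without continuity correction. The article gives no event rates, so a range of placebo rates is shown.

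**1. The plan's own sample size.** n per arm = 2(1.960 + 0.842)² × 6.1² / 3.91² = 38.2, rounded up to 39, or 78 in total. With 40 per arm the power is 0.818 (normal approximation) or 0.808 (t distribution). The stated 80 patients and at least 80% power are reproduced for the motor score. No corresponding figure is given for adverse events.

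**2. Power of the χ² test for harm.** For true rates p₀ (placebo) and p₁ (ambroxol), power is the sum over all 41 × 41 outcomes of Bin(x; 40, p₀) × Bin(y; 40, p₁), counting those with χ² > 3.84.

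| Placebo rate | Power, rate doubled | Power, rate tripled |
|---|---|---|
| 2.5% | 6% | 16% |
| 5% | 15% | 35% |
| 7.5% | 20% | 49% |
| 10% | 25% | 63% |
| 15% | 37% | 85% |
| 20% | 50% | 97% |
| 25% | 65% | above 99% |
| 30% | 80% | above 99% |

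Power falls to one half or less at a placebo rate of about 20% for a doubling and about 7.5% for a tripling. For 80% power the ambroxol rate must reach about 26% against 5%, 35% against 10%, or 49% against 20%.

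**3. Sensitivity to fewer patients.** With 36 per arm, 10% against 20% has power 22%, and 10% against 30% has 58%.

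**4. What a non-significant result leaves open.** Take 4/40 on placebo and 8/40 on ambroxol.
- χ² = 80 × (8 × 36 - 4 × 32)² / (40 × 40 × 12 × 68) = 1.57, p = 0.21.
- Wilson 95% limits: 0.105 to 0.348 for 8/40, and 0.040 to 0.231 for 4/40.
- Newcombe lower limit: 0.10 - √[(0.200 - 0.105)² + (0.231 - 0.100)²] = -0.06.
- Newcombe upper limit: 0.10 + √[(0.348 - 0.200)² + (0.100 - 0.040)²] = 0.26.

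The test is non-significant, and an excess of 26 percentage points is not excluded.

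**5. Events not seen on ambroxol.** For 0/40 the upper end of the exact two-sided 95% interval is 1 - 0.025^(1/40) = 8.8%.

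**6. Would an exact test help?** The uncorrected χ² test has a true size of about 1% to 6% at common rates of 2% to 20%, so it does not reject far too often. Fisher's exact test lowers power for harm: 5% against 15% falls from 35% to 18%, and 10% against 30% from 63% to 53%.

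**The case against.** The strongest case on the other side has three parts.

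- **Low power for adverse events is normal in a trial sized on efficacy.** This stands. The point does not ask for more patients. Low power is the reason to report an estimate with an interval rather than rely on a test.
- **Intervals, event categories and rules for sparse tables are often left to the full protocol or the analysis plan, which are not shown.** This stands in part. Those documents may add intervals. The article nevertheless states a method, and states publicly what the trial will show on safety, and the two do not match.
- **Safety does not rest on the χ² test alone.** There are weekly calls during titration, follow-up of all adverse events, and a Data and Safety Monitoring Board. This is true, but none of these compares the arms.

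Three stronger readings are tempting, and the documents do not support them. A reader might infer that the test misses any doubling or tripling in most trials; the table shows that this depends on the placebo rate and fails above about 20% and 8% respectively. A reader might infer that the investigators will treat non-significance as proof of safety; no sentence says so. A reader might also infer that χ² gives false alarms with sparse counts and must be replaced by Fisher's test. The article does not say whether a continuity correction applies, the uncorrected test's size is acceptable at the rates checked, and Fisher's test would make harm harder to detect.

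**Conclusion.** The concern holds in a limited form: a difference test at about 40 per arm cannot deliver the answer on safety that the abstract promises. It misses a doubling in at least half of trials at placebo rates up to about 20%, and a tripling up to about 7.5%, while larger contrasts are usually found. These figures rest on 1:1 allocation, full follow-up, the uncorrected χ² test and illustrative rates. Fewer evaluable patients or a continuity correction would lower the power further.

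The sample size for the primary endpoint is not in question, and neither the primary analysis nor the data collection is affected. The defect is the mismatch between a strong safety statement and a test-only comparison. It should be corrected because a better analysis of the same counts is available at almost no cost.

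**What to change.** In Statistical analyses, replace the χ² sentence with wording such as: *For each adverse-event category, the number of patients with at least one event will be given per arm, with the risk difference (ambroxol minus placebo) and its 95% score-based (Newcombe) confidence interval. For events not seen on ambroxol, the exact 95% upper limit of the rate will be given. Any p-value is supplementary. A non-significant difference will not be taken as evidence of safety.*

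In the abstract's Discussion paragraph, replace the safety promise with a statement that the trial will estimate the tolerability of this dose, with stated precision.

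The cost is two wording changes, with no extra patients, visits or data. The downside is a less favourable safety statement, since the intervals will be wide.
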